### Economic evaluation

To determine the short‐term cost‐effectiveness of the intervention, we will undertake a within‐trial incremental cost‐effectiveness analysis to assess the value for money afforded by the intervention over and above usual care at 6 months, using data collected during the trial.

The resources used to provide the e‐cigarette starter kit intervention will be recorded alongside the trial. This includes staff time and materials used to train clinicians delivering the intervention, the provision of the e‐cigarette starter kit and the staff time spent on consultations. All participants will have access to usual care, and the use of currently available smoking cessation aids will be collected using a service use questionnaire piloted in the feasibility study at baseline, and at the 1‐ and 6‐month follow‐ups. Additionally, the participants' wider healthcare resource use in primary and secondary care will also be collected using the service use questionnaire. To generate cost profiles for each participant, unit costs derived from both the trial records and the most recent national average cost data will be applied to the quantities of corresponding resources used [57, 58]. QALYs will be calculated based on responses obtained from the EQ‐5D‐5L questionnaire using the ‘area under the curve’ approach, serving as the primary health outcome for the cost‐effectiveness analysis [52, 59]. We will assess patterns of missing data and assess the impact of missingness using multiple imputation methods [60].

A decision‐analytic model developed at the University of York will be adapted to project the long‐term cost‐effectiveness beyond the trial period [61]. Lifetime smoking‐attributable healthcare cost and expected QALYs associated with the two trial arms will be estimated using Markov models. The model will account for annual background abstinence for people who smoke and relapse for quitters, and an annual discount rate of 3.5% will be applied to both costs and QALYs [53, 62, 63]. For detailed methods, please refer to a previously published article [61].

Both within‐trial and model‐based economic evaluation will be conducted from an NHS and personal social services perspective, as recommended by NICE guidance [53]. Incremental cost‐effectiveness ratios (ICERs) will be calculated based on the mean differences in costs and QALYs estimated using regression methods [53, 64]. The ICERs will then be compared with the NICE recommended maximum acceptable ICERs of £20,000–30,000 per QALY to determine the probability that the intervention is cost‐effective at 6 months [53]. Sensitivity analyses will be conducted to test the robustness of the findings.

### Adherence to and satisfaction with the e‐cigarette starter kit intervention

The proportions of participants adhering to and satisfied with the intervention will be calculated. Adverse events will also be assessed descriptively.

### Data and safety monitoring

A trial steering committee independent of the investigators, their employing organizations, funders and sponsors will provide overall supervision of the trial. They will monitor progress and advise on scientific credibility. A data monitoring committee will assess the progress of the trial. Safety monitoring and procedure manuals will be written before the commencement of the trial and distributed to relevant research staff. All adverse events will be recorded, and recurring (i.e. occurring in multiple participants more than once during the study period) adverse events will be reported to the data monitoring committee.

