### Sample size

We aim to recruit 616 participants, with 308 participants asigned to each group. Pooling the results of the only three RCTs comparing e‐cigarettes with placebo e‐cigarettes [15, 35, 36] yielded an expected effect size of risk ratio (RR) = 2.01 for 6‐month abstinence rates. We consider this estimate to be conservative as most of these trials used older, less effective first‐generation e‐cigarettes. In fact, recently published trials comparing active treatment (NRT) with a modern third‐generation e‐cigarette in the context of stop‐smoking services [12] found a superior effect of e‐cigarettes on 6‐month abstinence rates of RR = 1.63. Based on established effect estimates for NRT versus placebo from high‐quality trials [37], findings from this trial therefore indirectly suggest that, compared with placebo/usual care, third‐generation e‐cigarettes (as will be used in this trial) may increase 6‐month abstinence rates by nearly threefold (RR = 2.62). Given the low abstinence rates in the control conditions observed in the feasibility study [26], we revised the expected abstinence rates in the control (standard care) group from 7.7% (based on previous trials with people with mental illness) [38, 39] to 5.0%. Based on the feasibility study results (finding an absolute risk difference of 9.5%) [26] and the fact that a modern e‐cigarette is used, we assume an effect estimate of RR = 2.62, as found in more recent trials, to be most appropriate. We therefore expect an absolute predicted risk difference of 8.1%, assuming 6‐month abstinence rates of 5% in the control group and 13.1% in the intervention (e‐cigarette) group. A sample of 616 participants (308 per group) would provide more than 90% power to detect this effect, with an alpha level of 0.05 in two‐tailed analysis. This sample size would also provide 80% power to detect a more conservative effect of RR = 2.32 (intermediary between effect estimates from older and effect estimates from more recent trials using modern e‐cigarettes), with an absolute predicted risk difference of 6.6% at the 6‐month follow‐up (5.0% for the control group vs 11.6% for the treatment group).

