### Adverse events

At the 1‐ and 6‐month follow‐ups, participants will be asked to indicate if they have experienced any adverse events over the previous month and if these events stopped them from doing things they would normally do. These include the most common adverse events in previous trials, such as nausea, shortness of breath, throat/mouth irritation, increased appetite and headache [23].

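### The stated trigger for reporting adverse events to the data monitoring committee is repetition, not seriousness or imbalance between arms, and its wording can be read in two ways

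*Protocol article*

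**What the plan says.** The Data and safety monitoring section of the protocol article sets two statements side by side. The first is that "All adverse events will be recorded". The second is that "recurring (i.e. occurring in multiple participants more than once during the study period) adverse events will be reported to the data monitoring committee". The words in brackets are introduced as a definition, not as an example.

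The same section says of the committee's role that "A data monitoring committee will assess the progress of the trial", and it points to a further document: "Safety monitoring and procedure manuals will be written before the commencement of the trial and distributed to relevant research staff". The content of those manuals is not shown.

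On collection, the Adverse events section says that at the 1- and 6-month follow-ups "participants will be asked to indicate if they have experienced any adverse events over the previous month", and whether the events interfered with normal activities. On analysis, the section on adherence and satisfaction says "Adverse events will also be assessed descriptively".

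**The concern.** A monitoring committee needs to see events that are serious, even if there is only one, and events that are more frequent in one arm than in the other. The stated trigger uses neither property. It asks how often an event has happened and in how many people. The follow-up question on interference with normal activities gives some information on impact, but the trigger does not use it.

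The participants all have a diagnosed mental illness, and the Design and setting section expects those from secondary care to have more severe and enduring conditions. Adverse events and mental health symptoms are secondary outcomes. If site staff applied the sentence exactly as it stands, a single grave event would not qualify for the committee, while a minor symptom recurring in several people would. Two sites could also apply the phrase differently and forward different events.

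**Working it through.** The plan gives no figure for this rule, so there is none to reproduce. The check is of the wording, followed by a short illustration.

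**Step 1: the two readings.**
- Strict: at least two participants each have the event at least twice.
- Looser: the event type is seen more than once in total, across at least two participants.

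**Step 2: apply both readings to simple cases.**

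| Case | Strict | Looser |
|---|---|---|
| One serious event in one participant | not met | not met |
| Repeated events in one participant only | not met | not met |
| One event in each of ten participants, all in the intervention arm | not met | met |
| One event in each of ten participants, five per arm | not met | met |
| Two events in each of two participants | met | met |

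The first row does not depend on the reading, because one person is not multiple participants. Rows three and four show that the answer for scattered events depends wholly on the reading, and that arm never changes it.

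**Step 3: look for another stated route.** The places in the article that deal with adverse events or the committee are the assessment schedule (Table 1), Secondary outcomes measures, Adverse events, the section on adherence and satisfaction, and Data and safety monitoring. None states a second route to the committee. The safety manuals are the one place named where such a route might be.

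**Step 4: recall.** Questions at months 1 and 6, each about the preceding month, leave the months between without a planned question. The service use questionnaire (Table 3) also asks about the past month, so it does not fill the gap for hospital contacts.

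**Step 5: illustration of how far the readings differ.** The input from the plan is 308 participants in one arm (Sample size: "We aim to recruit 616 participants, with 308 participants asigned to each group"). Assumed, because the plan gives no rate: a probability p of the event in each of the two question windows, independent windows within a person, and recurrence visible only as an event in both windows.
- Probability that a participant is affected at least once: 1 − (1 − p)². Expected number affected: 308 × [1 − (1 − p)²].
- Looser reading, approximated as at least two participants affected: P(Binomial(308, 1 − (1 − p)²) ≥ 2).
- Strict reading: P(Binomial(308, p²) ≥ 2).

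| p | Expected affected | Looser met | Strict met |
|---|---|---|---|
| 0.5% | 3.1 | 81.3% | 0.003% |
| 1% | 6.1 | 98.5% | 0.05% |
| 2% | 12.2 | 99.99% | 0.7% |
| 5% | 30.0 | about 100% | 18% |
| 10% | 58.5 | about 100% | 81% |

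For example, at p = 1%: 1 − 0.99² = 0.0199, and 308 × 0.0199 = 6.1. The strict column is probably too low, because repeat events within one month would also count and symptoms are likely to be correlated within a person. The table shows only that the two readings can lead to very different reporting.

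**The case against.** The strongest reply is that the sentence says what is sent and does not say that everything else is withheld. The word 'only' is not in it. This is a condensed article, and serious-event definitions, expedited reporting and by-arm committee tables commonly sit in the full protocol, the safety manuals or a committee charter. This stands in part: a reader might infer that deaths or psychiatric admissions never reach the committee, or that it could not see a serious signal or an imbalance, and the documents do not support that. It does not remove the point, because the contrast between recording all events and reporting recurring ones makes the sentence work as a filter, and that filter is stated rather than left out.

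A second reply is that the looser reading is the more natural one, since the strict one would be an odd safety threshold. That is fair. A reader might infer that events in any number of different people, one each, trigger no report. This holds only on the strict reading and cannot be given as fact. But a rule that permits both readings needs rewording, and the looser reading still leaves out the single serious event.

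A third reply is that the questionnaires need not be the sole source, because all events are to be recorded. This stands. A reader might infer that adverse events are captured for just 2 of the 6 months (33%), or that recurrence between the questionnaires cannot be judged. Both assume that no spontaneous or site report is used, which the article does not say.

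The illustrative percentages rest on assumed rates and on independence between windows, and the conclusion does not depend on them.

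**Conclusion.** The point holds for the rule as the article states it. The trigger is repetition. It ignores seriousness and arm, and a single serious event fails it on either reading. For events occurring once in each of several participants, the outcome depends on how an ambiguous phrase is read. Recurrence between the two questionnaire windows is not systematically ascertained unless another route exists.

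The practical size cannot be fixed from the documents. If the safety manuals already send serious events and by-arm tables to the committee, what remains is an inconsistency in wording. If they follow the article's sentence, the committee would not routinely be sent single serious events. The change should be made in either case. It bears on safety oversight and leaves the sample size and the primary analysis as they are.

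**What to change.** In Data and safety monitoring, replace the filter on recurring events with two statements:

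1. The data monitoring committee receives all serious adverse events, whatever their frequency.
2. The committee receives a table by arm of all recorded adverse events, showing both the number of participants affected and the number of events.

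Reconcile this text with the safety monitoring and procedure manuals so that sites work to one rule. In the same place, say whether adverse events reported outside the month 1 and month 6 questionnaires are captured, and how.

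The cost is wording in the protocol and manuals, and one table per committee report. The table draws on events that the plan already records.

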### Ethics

Ethical approval was granted by Yorkshire and the Humber–South Yorkshire Research Ethics Committee in October 2023 (REC reference: 23/YH/0199) and Health Research Authority and Health and Care Research Wales (IRAS project ID: 328528).

### Dissemination

Results will be disseminated to key stakeholders and, more broadly, in several ways. These include: open‐access peer‐reviewed journal articles; presentation at key scientific meetings; feedback to trial participants via email or text message, which will include a link to blog posts regarding study results; and press releases. The data will be available on request to the principal investigators of the study.

## DISCUSSION

ESCAPE will be the first large‐scale RCT of e‐cigarette starter kits offered to adults who smoke with mental illness treated in the community in the UK. The trial is designed to provide insights into effective strategies for addressing tobacco use in this population, who face greater challenges compared with the general population owing to high dependence and limited access to support, relevant to researchers, policymakers and clinicians alike. If the intervention is shown to be both effective and cost‐effective, this will extend the evidence base for e‐cigarettes as a viable smoking cessation tool to adults who smoke with mental illness, with the potential to alleviate the substantial burden of tobacco‐related mortality and disease prevalent within this population and reduce associated health inequalities.

This is an important study that includes the use of biochemical validation of smoking abstinence, enhancing the reliability of the findings. However, there are some limitations that should be noted. First, the study is conducted in the UK, where the population with mental illness may differ from elsewhere, both in terms of healthcare access and specifically smoking cessation support, which is free to access in the UK. Additionally, this study may have limited generalizability to other countries, especially those that do not provide free smoking cessation services as part of the healthcare system and those where e‐cigarettes are regulated differently to the UK. Furthermore, owing to the nature of the intervention and study design, participants, researchers and clinical staff administering the intervention cannot be blinded. We will only recruit adults who smoke with a diagnosis of mental illness treated in the community and who are willing to address their smoking behaviour, either by attempting to quit or by reducing their cigarette consumption. Additionally, we will not conduct any analyses specifically focusing on individuals with different types of mental illness.

## CONCLUSIONS

The ESCAPE trial will be the first large‐scale study in the UK to explore the effectiveness of providing an e‐cigarette starter kit as a harm reduction and smoking cessation tool for adults who smoke with mental illness treated in the community. The finding of this study will provide much needed information to strengthen the evidence base for effective intervention strategies to address tobacco use in this population and reduce associated health inequalities.

## CLINICAL TRIAL REGISTRATION

ISRCTN17691451.

## Data Availability

When the trial is completed the data will be kept in a repository for 10 years and will be available upon request.
